### Overview of the study design

This is an international trial consisting of 4 parallel randomized, double-blind, placebo-controlled, multi-center phase II studies to evaluate the efficacy and safety of regorafenib in patients with histologically proven metastatic and/or unresectable STS after failure or intolerance to doxorubicin (or other anthracyclin). Patients must have shown objective disease progression at study entry.

Patients will be registered at the Clinical Research Unit of the Oscar Lambret Cancer Center prior to start the treatment, and after verification of eligibility criteria. Patients will be randomized to receive oral regorafenib or placebo in a 1:1 ratio, until disease progression (RECIST 1.1 guidelines), death, unacceptable toxicity or withdrawal of consent for any reasons. Patients receiving placebo who experience disease progression may be offered open-label regorafenib after checking of eligibility criteria and real-time central radiological review of imaging to confirm progression according to RECIST 1.1 (Figure 1).

**Figure 1 Fig1:**
[figure not shown]
**Trial Design: 4 parallel phase II double-blind placebo-controlled phase II trials.**

An independent data monitoring committee is planned to assess the risk/benefit ratio after enrollment of the 50 first patients.

The study is composed of 3 periods:Screening PeriodTreatment Period during which either regorafenib or placebo will be administered (The Treatment Period includes an end of treatment visit and a 30 (+/-7) day follow-up period that ends with a safety follow-up visit).Survival Follow-up Period during which survival status will be monitored

During the Screening Period and the Treatment Period, patients are considered “on-study”; during the Survival Follow-up Period, patients are considered “off-study”. During the treatment period the tumour assessment will be done every month during the 4 first months and then every 3 months. Study assessments is summarized in Table 1 (Flow-chart).

**Table 1 Tab1:** **Study procedures and flow-chart**

	Screening 14 days	d1, d30, d60, d90, d120	After the 4^th^month, every 3 months until tolerance or progession
Physical exam	X	X	X
Safety	X	X	X
Availbility of tumour sample	X		
Thoracic and abdominopelvic CT-Scann	X	X	X
Echocardio or MUGA	X		X
Hematology INR TCA	X	X	X
Biochemistry (1)	X	X	X
Urine Dipstick	X	X	X
Serum sample for TR programm		X	

(1) Serum creatinine, Glomerular filtration rate (Cockroff and Gault), AST, ALT, Bilirubin, Alkaline phosphatases, Amylase and lipase, CPK.

The patients will be randomly allocated to one of the treatment described above.Regorafenib: 4 tablets, once daily, 3 weeks on/1 week off

+ Best Supportive Care

OrPlacebo: 4 tablets, once daily, 3 weeks on/1 week off

+ Best Supportive Care

until progression or unacceptable toxicity in both arms.

Best supportive care includes any method to preserve the comfort and dignity of the patients and excludes any disease-specific anti-neoplastic agent.

Details on dose-adaptations, prohibited concomitant medications and the study flow-chart could be obtained by request to the corresponding author.

### Eligibility criteria

All the following must be met at the time of screening.Age ≥18 years of ageHistological documentation of soft tissue (including uterus) sarcoma with available FFPE blocks obtained.Prior treatment with doxorubicin or other anthracyclinMetastatic disease not amenable to surgical resection with curative intentDocumentation of progression before study entryMeasurable disease, defined as at least 1 unidimensionally measurable lesion on a CT scan as defined by RECIST 1.1.Eastern Cooperative Oncology Group (ECOG) performance status ≤1Life expectancy of at least 3 monthsAdequate bone marrow, renal, and hepatic function, as evidenced by the following within 7 days of study treatment initiation:Absolute neutrophil count (ANC) ≥1,500/mm3Platelets ≥100,000/mm3Hemoglobin ≥9.0 g/dLSerum creatinine ≤1.5 x upper limit of normal (ULN)Glomerular filtration rate (GFR) ≥30 ml/min/1.73 m2AST and ALT ≤2.5 x ULN (≤5.0 × ULN for patients with liver involvement of their cancerBilirubin ≤1.5 X ULNAlkaline phosphatase ≤2.5 x ULN (≤5 x ULN with liver involvement of their cancer)Amylase or lipase ≤1.5 x ULNSpot urine must not show 1+ or more protein in urine or the patient will require a repeat urine analysis. If repeat urine analysis shows 1+ protein or more, a 24-hour urine collection will be required and must show total protein excretion <1000 mg/24 hoursINR/PTT ≤1.5 x ULN - Patients who are therapeutically treated with an agent such as warfarin or heparin will be allowed to participate provided that no prior evidence of underlying abnormality in coagulation parameters exists. Close monitoring of at least weekly evaluations will be performed until INR/PTT is stable based on a measurement that is pre-dose as defined by the local standard of careWomen of childbearing potential and male patients must agree to use adequate contraception for the duration of study participation and up to 3 months following completion of therapy. Adequate contraception is defined as any medically recommended method (or combination of methods) as per standard of care.Recovery to National Cancer Institute-Common Terminology Criteria for Adverse Events (NCI-CTCAE) v4.0 Grade 0 or 1 level or recovery to baseline preceding the prior treatment from any previous drug/procedure related toxicity (except alopecia, anemia, and hypothyroidism).In the assessment of the investigator, patient is able to comply with study requirementsSigned, IRB-approved written informed consent as approved by ethical and regulatory committee: French Ethical Committee (“*Comité de Protection des Patients Nord-Ouest IV”*; date of approval 21th March 2013), and Austrian Ethical Committee (“Ethik Kommission Medizinische Universität Wien (n° 1376/2013)) and French Drug Agency (“*Agence Nationale de Sécruité du Médicament*”; date of Approval 8^th^ March 2013).

#### Exclusion criteria

Patients who meet any of the following criteria at the time of screening will be excluded from the study.More than 3 lines of systemic treatment for metastatic sarcomaSome particular histologies: GIST, osseous sarcoma, embryonnal or alveolar rhabdomyosarcoma)Primary bone sarcomaPrior treatment with regorafenibKnown history of or concomitant malignancy likely to affect life expectancy in the judgment of the investigatorPregnant or breastfeeding patients. Women of childbearing potential must have a pregnancy test performed a maximum of 7 days before start of treatmentMajor surgical procedure, open biopsy, or significant traumatic injury within 28 days before start of Day 1 of treatmentActive cardiac disease including any of the following: Congestive heart failure (New York Heart Association [NYHA]) ≥ Class 2, Unstable angina (angina symptoms at rest), new-onset angina (begun within the last 3 months), Cardiac arrhythmias requiring anti-arrhythmic therapy (beta blockers or digoxin are permitted)Uncontrolled hypertension. (Systolic blood pressure >150 mmHg or diastolic pressure >90 mmHg despite optimal medical management)Arterial or venous thrombotic or embolic events such as cerebrovascular accident (including transient ischemic attacks), deep vein thrombosis, or pulmonary embolismOngoing infection > Grade 2 according to NCI Common Terminology Criteria for Adverse Events version 4.0 (CTCAE v. 4.0)Known history of human immunodeficiency virus (HIV) infectionKnown history of chronic hepatitis B or CPatients with seizure disorder requiring medicationHistory of organ allograftEvidence or history of bleeding diathesis. Any hemorrhage or bleeding event > Grade 4 within 4 weeks of start of treatmentNon-healing wound, ulcer, or bone fractureRenal failure requiring hemo- or peritoneal dialysisDehydration according to NCI-CTC v 4.0 Grade >1Substance abuse, medical, psychological, or social conditions that may interfere with the patient’s participation in the study or evaluation of the study resultsKnown hypersensitivity to any of the study drugs, study drug classes, or excipients in the formulation including lactoseInterstitial lung disease with ongoing signs and symptoms at the time of informed consentInability to swallow oral medications, Any malabsorption conditionPleural effusion or ascites that causes respiratory compromise (Grade 2 dyspnea)Unwilling to provide consent for genetic studies of tumor, whole blood, or plasma specimens

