#### Analysis sets

The following patient populations will be considered in the final analyses.Intention-to-treat population: All randomized patients will be analyzed in the arm they were allocated by randomization.Per protocol population: All patients who are eligible and have started their allocated treatment (at least one dose of the study drug)Safety population: All patients who have started treatment (at least one dose of the study drug)

A patient will be considered to be eligible if he/she did not have any major deviations from the patient entry criteria listed in chapter 3 of the protocol. Eligibility will be assessed by the Study Coordinator based on the review of each patient file.

The primary analysis will be conducted on the Intention-to-treat population.

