## Discussion

### Accrual

The study is enrolling since June 2013 (at the time of the preparation of this paper in 26 sites in France and Austria) The accrual is faster than expected. Per 1^st^ of May 2014, 2 strata are already closed to recruitment (leiomyosarcomas and other sarcomas). The number of enrolled patients is 152 (out of 192). The recruitment is still ongoing for synovial sarcoma and liposarcoma strata. According to the recruitment rate, the study will be definitely closed to recruitment between December 2014 and February 2015 (Figure 2).

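### The bleeding exclusion is set above Grade 4, which no living patient can meet, so it does not screen out a recent Grade 3 or Grade 4 bleed

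*Protocol article*

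**What the plan says.** The Exclusion criteria section applies its list to living patients being screened: "Patients who meet any of the following criteria at the time of screening will be excluded from the study". One item has two parts. The first excludes a bleeding diathesis, present or past, with no grade. The second excludes "Any hemorrhage or bleeding event > Grade 4 within 4 weeks of start of" treatment.

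The bleeding clause does not name its scale. NCI-CTCAE v4.0 is the only adverse-event grading scale in the article. It is named for toxicity in Study endpoints, for recovery from earlier toxicity in Eligibility criteria, and for infection and dehydration in Exclusion criteria.

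No other section repeats the bleeding cut-off or gives a different one.

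**The concern.** A four-week window shows that the authors wanted a washout after a serious bleed. With the cut-off as printed, that washout cannot operate: a patient with a life-threatening bleed two weeks before the first dose does not meet the clause.

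What is at stake is patient safety and clear eligibility rules. Regorafenib inhibits VEGFR-1, -2 and -3 (Investigational treatment), and this is the only criterion that sets a waiting period after a bleed as such. Nothing in the primary intention-to-treat comparison depends on it.

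**Working it through.** There is no power or sample-size figure to reproduce. The check is a logical one, followed by two head counts.

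**1. Which grades the clause catches.** CTCAE v4.0 runs from 1 to 5, with 5 meaning death. The article does not print that definition; it belongs to the scale the protocol adopts. A patient at screening can have had a bleed of Grade 1, 2, 3 or 4.

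| Criterion | Cut-off | Grades caught in living patients |
|---|---|---|
| Bleeding, as printed | > 4 | none |
| Infection, same list | > 2 | 3, 4 |
| Dehydration, same list | > 1 | 2, 3, 4 |
| Bleeding, smallest correction | ≥ 4 | 4 |
| Bleeding, stricter option | ≥ 3 | 3, 4 |

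The two neighbouring graded items have cut-offs that a living patient can meet. The bleeding item does not.

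**2. Whether the sign was lost in text extraction.** This is unlikely, because the same list keeps the other sign intact: "Congestive heart failure (New York Heart Association [NYHA]) ≥ Class 2".

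**3. Whether another criterion fills the gap.** Take a tumour bleed of Grade 4 that stopped two weeks ago without major surgery, in a patient who otherwise qualifies.

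- Bleeding diathesis: this is a predisposition; a single tumour bleed need not show one.
- Hemoglobin: at least 9.0 g/dL is enough to pass.
- Platelets and INR/PTT: these can be normal. Patients on therapeutic warfarin or heparin may also enter, under conditions.
- ECOG status and life expectancy: neither refers to a bleed that has resolved.
- Major surgery or significant trauma within 28 days: not triggered in this case.
- Toxicity recovery: this covers only recovery "from any previous drug/procedure related toxicity (except alopecia, anemia, and hypothyroidism"). A tumour bleed is neither drug- nor procedure-related, and anemia is excepted.

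None of these objective criteria excludes the patient.

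**4. How far a forward correction reaches.** The Accrual section reports 152 of 192 patients enrolled on 1 May 2014.

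- Still to enrol: 192 − 152 = 40. The section says "The recruitment is still ongoing for synovial sarcoma and liposarcoma strata".
- Placebo patients who could reach the open-label eligibility check: at most 192 / 2 = 96 over the whole trial under 1:1 allocation, and fewer if some have already crossed over.

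Both numbers show whom a correction could reach. Neither is a count of patients harmed or wrongly enrolled.

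**The case against.** The printing error itself is hard to dispute. The case on the other side is that it matters less than it seems.

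- **Grade 3 may never have been meant.** The document does not say which cut-off was intended. If it was at least Grade 4, a Grade 3 bleed would be admitted by design. This stands: it remains true that the printed clause lets Grade 3 through, but only the Grade 4 gap follows from the text whatever the intent. The stricter cut-off is for the clinical team to decide.
- **Other safeguards exist.** The 28-day rule imposes a wait on bleeds that come with major trauma or surgery. Non-healing ulcers and cerebrovascular accidents are excluded, and the investigator may exclude a patient for a medical condition that could interfere with participation. This narrows the gap to a resolved, non-traumatic bleed, managed without major surgery, that the investigator does not judge disqualifying. It does not close it, and discretion is not a rule.
- **The safety link is thinly documented.** The article does not say that VEGFR inhibition raises bleeding risk, and hemorrhage is not among the adverse events it lists from the two earlier phase III trials. Those lists cover only the most common events, however, and by writing the exclusion the authors showed that they were concerned. The size of the risk cannot be read from the article.
- **The open-label check may not use this list.** The Overview of the study design says placebo patients who progress "may be offered open-label regorafenib after checking of eligibility criteria" and central confirmation of progression, without saying which criteria. The figure of 96 is therefore a ceiling that depends on this list being re-applied.
- **The error may be only in the article.** Analysis sets refers to "the patient entry criteria listed in chapter 3 of the protocol", which is not shown. If chapter 3 is right, no site screened patients under the wrong cut-off. This stands, and it determines the remedy.

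**Conclusion.** The concern holds. As printed, the graded part of the bleeding exclusion catches none of the four grades a living patient can have, so it excludes neither a Grade 3 nor a Grade 4 bleed in the four weeks before treatment. Other criteria reduce the practical gap but leave at least a resolved, non-traumatic Grade 4 tumour bleed uncovered.

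The conclusion assumes that the clause is graded on CTCAE v4.0, the only such scale in the article, and that Grade 5 means death on it. How many patients are affected is unknown, because the article gives no rate of recent severe bleeding and chapter 3 is not available. This is a wrong eligibility threshold that should be fixed for safety; it does not change the sample size, the type I error or the intention-to-treat result.

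**What to change.** 1. Compare the clause with chapter 3 of the full protocol.
2. If chapter 3 has a workable cut-off, correct the article only.
3. If chapter 3 has the same text, amend it to at least Grade 4, or to at least Grade 3 if the clinical team confirms that this was intended. Name CTCAE v4.0 in the clause.
4. Apply the amended cut-off to patients not yet enrolled and to the eligibility check before open-label regorafenib.
5. Do not re-judge the per-protocol status of patients already enrolled against the later cut-off.

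The cost is one symbol or digit in one clause, plus the name of the scale. If the full protocol is affected, add a short amendment and a notice to sites. No new data are collected and the analysis does not change.

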### Statistical considerations

#### Statistical hypothesis – Sample size calculation

The primary endpoint is progression-free survival (PFS) according to RECIST 1.1 guidelines and with central radiological review. The sample size is calculated on the basis of the primary endpoint. The study consists of 4 parallel phase II trials in 4 sub-populations defined by histology: liposarcoma, leiomyosarcoma, synovial sarcoma and other sarcomas. Recent literature data suggest that PFS with placebo is about 1.6 months [14]. The expected PFS with regorafenib is 4.6 months. Statistical assumptions for the 3 most frequent histological subtypes (liposarcoma, leiomyosarcoma and other sarcomas) are: PFS0 = 1.6, PFS1 = 4.6, alpha = 0.1 (one-sided) and power (1-β) = 0.95, the sample size is 50 patients per stratum (30 expected events). For the Synovial sarcoma stratum, based on its low prevalence and in order to not delay significantly the duration of the study, lower power is considered acceptable and only 25 patients will randomized in this cohort (Alpha = 0.10, Beta = 0.20, 16 events and 25 patients).

At the end, the total number of patients is calculated as follows: (50x3) + 25 = 176 (+10% of non-valuable patients: 192)

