**Methods/design:**

We are conducting an international trial (France, Austria and Germany) consisting in 4 parallel double-blind placebo-controlled randomized (1/1) phase II trials to assess the activity and safety of RE in doxorubicin-refractory STS (ClinicalTrials.gov: NCT01900743). Each phase II trial is dedicated to one of the 4 following histological subgroups: liposarcoma, leiomyosarcoma, synovial sarcoma and other sarcoma. Within each randomized trial the following stratification factors will be applied: countries and prior exposure to pazopanib. Key-eligibility criteria are: measurable disease, age ≥18, not > 3 previous systemic treatment lines for metastatic disease, metastatic disease not amenable to surgical resection. The primary endpoint is progression-free survival (PFS) according to central radiological review. Secondary endpoints are: Toxicity (NCI-CTC AE V4.0); time to progression; Growth modulation index in pts receiving RE after randomization; 3 and 6 months PFS-Rates, best response rate and overall survival. Each phase II trial will be separately analyzed. In 3 trials, statistical assumptions are: PFS0 = 1.6 & PFS1 = 4.6 months; 1-sided α = 0.1; β = 0.05 with a total sample size of 192 pts. To take into account the rarity of synovial sarcoma, the statistical assumptions are: PFS0 = 1.6 & PFS1 = 4.6 months; 1-sided α = 0.1; β = 0.2 Tumor assessment is done monthly during the 4 first months, and every 3 months thereafter. After central radiological confirmation of tumor progression, an optional open-label option is offered to eligible patients.

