#### Randomization and stratification

Patients will be centrally randomized to receive regorafenib or placebo, in a double blind fashion, and in a 1:1 ratio respectively. Four strata will be identified: leiomyosarcoma (50 patients), liposarcoma (50 patients), other sarcoma (50 patients) and synovial sarcoma (26 patients). A permuted blocks randomization technique will be used for treatment allocation. Within the 4 strata, stratification factors will be: prior exposure to pazopanib (yes/no) and countries.

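### The sample-size sum is off by one, and the synovial cohort has two sizes: the printed 176 needs 26 synovial patients, the printed 192 needs 25

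*Protocol article*

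**What the plan says.** For liposarcoma, leiomyosarcoma and other sarcomas, the section Statistical hypothesis – Sample size calculation states that "the sample size is 50 patients per stratum (30 expected events"). For synovial sarcoma it accepts lower power because the disease is rare: "only 25 patients will randomized in this cohort (Alpha = 0.10, Beta = 0.20, 16 events and 25 patients"). It then adds up the four cohorts and applies an allowance for patients who cannot be evaluated: "50x3) + 25 = 176 (+10% of non-valuable patients: 192").

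The section that follows, Randomization and stratification, lists the four cohorts again. Leiomyosarcoma and liposarcoma have 50 each, followed by "other sarcoma (50 patients) and synovial sarcoma (26 patients").

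The abstract, under Methods/design, reads: "In 3 trials, statistical assumptions are: PFS0 = 1.6 & PFS1 = 4.6 months; 1-sided α = 0.1; β = 0.05 with a total sample size of 192 pts". Its next sentence gives the synovial assumptions without a sample size. The Accrual section and the translational research workflow also use 192, as the enrolment target and as the number of tumour samples.

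**The concern.** The printed equation is false, and two adjacent sections of current text disagree on the size of one cohort. The four trials are to be analysed separately, and the Accrual section shows that they close to recruitment separately: two had closed while the synovial and liposarcoma cohorts were still open. Each cohort therefore needs one planned size, and the smallest and lowest-powered of the four has two.

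The chain from cohort sizes to total is also inconsistent at both steps, so a reader cannot work back from the totals to the intended synovial size. The abstract adds to this: read literally, it makes 192 the size of three trials.

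**Working it through.** **Inputs.** Three cohorts of 50; a synovial cohort of 25 (sample-size section) or 26 (randomization section); an allowance of +10%; printed totals of 176 and 192. For the side check on events: median PFS of 1.6 and 4.6 months, one-sided alpha 0.10, power 0.95 or 0.80, 1:1 allocation, 30 and 16 events.

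**Step 1: the sum.**
- With 25: 3 x 50 + 25 = 175.
- With 26: 3 x 50 + 26 = 176.

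The printed 176 is reproduced only with 26, although the equation prints 25.

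**Step 2: the allowance, read literally as x 1.10.**
- From 175: 175 x 1.10 = 192.5, which is 192 rounded down.
- From 176: 176 x 1.10 = 193.6, which is 194 rounded up.

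The printed 192 is therefore reproduced from 175 and a synovial size of 25. By cohort, the same 10% gives 3 x 55 + 27.5 = 192.5. From the printed 176, 192 is an allowance of 192/176 - 1 = 9.1%, not 10%.

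**Step 3: the two chains side by side.**

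| Synovial size | Sum | x 1.10 | Printed figure matched |
|---|---|---|---|
| 25 | 175 | 192.5 | 192 (rounded down), not 176 |
| 26 | 176 | 193.6 | 176, not 192 |

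No single synovial size gives both printed totals at 10%.

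**Step 4: the abstract.** Three cohorts of 50 make 150, or 165 with 10% added. The 192 can only be the four-trial total, as the sample-size section derives it.

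**Step 5: does it touch power?** Under exponential PFS the hazard ratio is 1.6/4.6 = 0.348, and ln(0.348) = -1.056. Schoenfeld's formula is d = 4(z_alpha + z_beta)^2 / (ln HR)^2.
- Power 0.95: 4 x (1.2816 + 1.6449)^2 / 1.115 = 30.7, so 31 events against 30 stated. Power at 30 events is 0.946.
- Power 0.80: 4 x (1.2816 + 0.8416)^2 / 1.115 = 16.2, so 17 events against 16 stated. Power at 16 events is 0.797.

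The event targets agree with the stated assumptions to within one event. They do not depend on whether the synovial cohort is 25 or 26, or on whether the total is 192 or 194.

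**The case against.** The strongest reply is that this is a one-patient slip in an intermediate figure. The total that the study works to is 192. It is the same in the abstract, the sample-size section, the Accrual section and the translational workflow, and it follows from the stated cohorts of 50, 50, 50 and 25 with 10% added. The abstract's wording is loose, but the sample-size section makes clear that 192 covers four cohorts. Log-rank power depends on events, and those targets stand. All of this is correct, and it limits the size of the point. It does not remove the false equation or the two synovial sizes.

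Two stronger readings are tempting, and the document supports neither.

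- **That 192 cannot be obtained at all.** It can: 175 x 1.10 = 192.5, rounded down. What fails is only the step from the printed 176.
- **That the allowance is too small.** Dividing by 0.9 gives 194.4 (from 175) or 195.6 (from 176), and 10% loss from 192 leaves 172.8, which is 2.2 or 3.2 below the two sums. But the article writes +10%, for which multiplying by 1.10 is the literal reading; dividing by 0.9 is a different convention. The gap averages less than one patient per cohort over four separately analysed trials (for a cohort of 50, 55 x 0.9 = 49.5). The primary analysis also keeps all randomized patients, so those called non-evaluable are not removed from it.

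Nor is the lack of a printed enrolment cap per cohort a finding. A condensed article may leave that to the full protocol.

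**Conclusion.** The point holds as an inconsistency in the stated sample size. The sum is misprinted by one, the synovial cohort is 25 in one section and 26 in the next, and the printed totals of 176 and 192 come from different synovial sizes. The abstract attaches the four-trial total to three trials.

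The size is one patient in the synovial cohort and about two in the total (192 against 194). This rests on reading +10% as a multiplication by 1.10. A reader might infer that the trial is under-recruited or underpowered; the event check does not bear that out. The document does not show which synovial size was intended. Thirteen per arm under 1:1 allocation would suit 26, but the final total suits 25, so the authors have to settle it.

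**What to change.** State one synovial size in both the sample-size and the randomization sections, and make the chain follow from it:

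- **25:** 3 x 50 + 25 = 175, then 192 (rounded down from 192.5). Change 26 to 25 in the randomization section.
- **26:** 3 x 50 + 26 = 176, then 194 (rounded up from 193.6). Change 25 to 26 throughout the sample-size section, and carry 194 into the abstract, the Accrual section and the translational workflow.
- **26, keeping the total:** 176, then 192, with the allowance described as about 9%.

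In the abstract, give the total once for all four trials, separately from the assumptions of the three larger ones.

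The cost is a text correction. The first and third options leave the enrolment target at 192 and need no further patients; the second raises the stated total by two. No event target, significance level or analysis changes under any of them.
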